### Sample size

According to earlier studies and the previous work of our research team, the effective rates of stereotactic EEG-guided RF-TC, MRI-guided stereotactic LITT, and resective surgery are similar, and the rates of postoperative neurological impairment are 2%, 2%, and 11%. We expect to use a one-sided 95% confidence interval, a noninferiority limit of 10%, and an expected withdrawal rate of 20%. Therefore, we expect to enroll a total of 240 patients in this study. Patients will be recruited from outpatient and MDT with strict inclusion criteria.

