## Abstract

**Background:**

This protocol describes the design of a multicenter randomized controlled trial of robot-assisted stereotactic lesioning versus epileptogenic foci resection. Typical causes of focal epilepsy include hippocampal sclerosis and focal cortical dysplasia. These patients usually present with drug resistance and require surgical treatment. Although epileptogenic foci resection is still the most commonly used treatment for such focal epilepsy, there is increasing evidence that epileptogenic focus resection may lead to neurological impairment. The treatment of epilepsy with a robot-assisted stereotactic lesioning mainly includes two new minimally invasive surgical methods: radiofrequency thermocoagulation (RF-TC) and laser interstitial thermal therapy (LITT). Seizure-free is less likely to be achieved by these two procedures, but neurologic preservation is better. In this study, we aimed to compare the safety and efficacy of RF-TC, LITT, and epileptogenic foci resection for focal drug-resistant epilepsy.

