### Outcomes

#### Primary outcome

The primary outcome is the participant’s seizure remission rate, which was defined by the following formula:$$\mathrm{Seizure\,remission\,rate}=\frac{\mathrm{Baseline\,seizure\,frequency}(\mathrm{per\,month}) -\mathrm{ Post}-\mathrm{op\,seizure\,frequency }(\mathrm{per\,month})}{\mathrm{Baseline\,seizure\,frequency}(\mathrm{per\,month})}\times 100\%$$

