### Statistical analysis

Statistical analysis will be mainly performed by researchers from Sanbo Brain Hospital, Capital Medical University, using the SAS 9.3 (SAS Institute Inc., Cary, NC, USA) software. Take the test level *α* = 0.05. The Kolmogorov-Smirnov test will be used to test whether the variables will be normally distributed. Measurement data conforming to normal distribution will express as mean ± standard deviation (‾X ± s), and measurement data not conforming to normal distribution will be expressed as interquartile range *M* (Q25, Q75). The *t*-test will be used to compare the normal distribution of continuous variables. The rank sum test will be used to compare the continuous variables that do not conform to the normal distribution. The chi-square test will be used to compare the categorical data. Univariate and multivariate methods will be used to analyze the preoperative and operative factors associated with seizure-free. Analysis of the primary outcome will be by intention-to-treat.

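### The sample size of 240 cannot be reproduced without unstated or altered inputs and is not justified for the primary outcome, seizure remission rate

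*Protocol article*

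**What the plan says.** The Primary outcome section names the "seizure remission rate, which was defined by the following formula", and the formula is each participant's percent reduction from baseline in monthly seizure frequency. That is a continuous measure. Neurologic impairment is listed under Secondary outcomes.

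The Sample size section states that "the effective rates of stereotactic EEG-guided RF-TC, MRI-guided stereotactic LITT, and resective surgery are similar", with no value, and that "the rates of postoperative neurological impairment are 2%, 2%, and 11" per cent. It continues: "We expect to use a one-sided 95% confidence interval", then "a noninferiority limit of 10%, and an expected withdrawal rate of 20" per cent. From this it concludes that "we expect to enroll a total of 240 patients in this study". It does not give a power, the outcome to which the limit applies, or whether the contrast is pooled lesioning or each technique against resection.

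The Statistical analysis section adds "Take the test level *α* = 0.05" without sidedness. The abstract's Background says of radiofrequency thermocoagulation and laser therapy: "Seizure-free is less likely to be achieved by these two procedures".

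**The concern.** The paragraph is set out as a derivation, so a reader should be able to get from its inputs to 240. The numeric inputs concern a secondary outcome, and the limit is attached to nothing. The wording invites the reader to think that 240 supports a 10-point noninferiority claim on efficacy, because efficacy is what is assumed to be alike across groups. No input in the paragraph shows that it does.

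Interpretation is at stake. If the efficacy comparison has low power, an inconclusive result may be read as inferiority, or a wide interval around zero as equivalence. The assumption of alike efficacy also matters because noninferiority power falls quickly when the new treatment is even slightly worse.

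**Working it through.** **Inputs.** From the Sample size section: 240 enrolled, 20% withdrawal, limit 10 points, one-sided 95% interval (z = 1.645), impairment 2% v 11%. From Randomization and blinding: 1:1 lesioning to resection, then 4:1 within lesioning. Evaluable per arm: 240/2 × 0.8 = 96. Assumed: 80% power (z = 0.842), so (1.645 + 0.842)² = 6.18; and effective rates of 50 to 80%, borrowed from the range for seizure freedom after surgery in the main Background.

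**1. Trying to reproduce 240.**
- Noninferiority on impairment as written: 6.18 × (0.02×0.98 + 0.11×0.89) / (0.10 + 0.09)² = 6.18 × 0.1175 / 0.0361 = 20.1, so 21 per arm; 42/0.8 = 52.5, about 53 enrolled.
- One-sided superiority on impairment, which the section does not state: 6.18 × 0.1175 / 0.09² = 89.7, so 90 per arm (92 with pooled variance); 225 to 230 enrolled.
- Noninferiority on impairment with both groups at the averaged rate of 6.5% and one-sided 0.025: (1.960 + 0.842)² × 2 × 0.065 × 0.935 / 0.10² = 95.4, so 96 per arm and exactly 240. This replaces the stated alpha, discards the stated 2% v 11% difference and needs an unstated power. At the stated one-sided 0.05 it gives 76 per arm, 190 enrolled.

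The literal inputs miss 240 more than fourfold. The readings that come near it change or add inputs, and all of those shown concern impairment.

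**2. If the limit applies to a binary effective rate p, equal in both groups.** n per arm = 6.18 × 2p(1−p) / 0.10².
- p = 0.50: 310 per arm, 775 enrolled.
- p = 0.65: 282 per arm, 705 enrolled.
- p = 0.80: 198 per arm, 495 enrolled.

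Power at 96 per arm = Φ(0.10/√(2p(1−p)/96) − 1.645): 40%, 42% and 53% respectively. At p = 0.50 the one-sided margin of error is 1.645 × √(0.5/96) = 11.9 points, so even identical observed rates would not meet the limit.

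If lesioning is truly 5 points lower, the numerator becomes 0.05. Power is then 17% (50% v 45%) to 21% (80% v 75%).

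**3. If the limit applies to the primary outcome as defined (mean percent reduction).** Power at 96 per arm = Φ(10/(SD√(2/96)) − 1.645).

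| SD (points) | Power |
|---|---|
| 20 | 97% |
| 25 | 87% |
| 28 | 80% |
| 30 | 75% |
| 40 | 53% |

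The largest SD giving 80% is 10 / (2.487 × √(2/96)) = 27.9 points. The document gives no SD.

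**4. Single-technique contrasts.** The 4:1 split leaves about 77 and 19 evaluable. For binary rates of 50 to 80%, power is 37 to 50% for radiofrequency v resection and 20 to 26% for laser v resection. The contrast therefore has to be named.

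**5. Impairment as a secondary comparison.** For 2% v 11% at 96 per arm, Fisher's exact test has 75% power one-sided and 66% two-sided. The normal approximation gives about 82% and 72%, which is optimistic with only about two expected events in the lesioning arm (96 × 0.02 = 1.9).

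**The case against.** The best defence is that 240 may be adequate for the outcome as defined. The primary outcome is continuous, and with an SD of about 28 points or less 96 per arm meets a 10-point limit with 80% power. A binary rate near 91.5% would also do. The 40 to 53% figures depend on a binary rate that the article never defines and on a range borrowed from background text on seizure freedom. All of this stands. A reader might infer that 240 cannot deliver a noninferiority comparison of efficacy; the document does not support that, because the answer turns on an SD it does not give.

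A second defence is that 240 does have a route: the averaged-rate calculation gives it exactly, and one-sided superiority on impairment at 230 could have been rounded up. So it would be wrong to say that no calculation yields 240, or that superiority is the only one near it. But each route alters or supplies inputs, and neither concerns the primary outcome.

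Third, a reader might see a flat contradiction between the abstract and the Sample size section. The abstract speaks of seizure freedom and the Sample size section of undefined effective rates; the Discussion itself separates seizure-free from responder rates. Lower seizure freedom can coexist with a like percent reduction. This is a tension to reconcile, not a proven contradiction. Nor does the abstract give the size of any deficit, so it cannot be said that noninferiority would almost never be shown.

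**Conclusion.** The point holds in this form: 240 cannot be reproduced from the section without unstated or altered inputs, and it is not justified for the seizure remission rate. At an assumed 80% power the literal impairment reading gives about 53 enrolled, and a binary efficacy reading gives 495 to 775 for rates of 50 to 80%. For the continuous primary outcome 240 may be enough or may not: power runs from 97% at SD 20 to 53% at SD 40. These results rest on normal approximations, one-sided 5%, 1:1 pooled lesioning v resection and 20% loss.

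This is more than detail left to a fuller document, because the article prints a derivation and its inputs do not lead to the printed result. It should be corrected, since readers will rely on the figure when they judge an efficacy result.

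**What to change.** Keep 240 and rewrite the Sample size section for the primary outcome:

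- Say that the 10-point limit applies to the seizure remission rate for pooled lesioning v resection, name the time point (the abstract lists 3 months, 6 months and 1 year), and give the assumed SD with its basis.
- State the power that 96 evaluable per arm delivers: about 97% at SD 20, 80% at SD 28, 75% at SD 30 and 53% at SD 40.
- If a binary effective rate is meant instead, define it and state about 40 to 53% power for equal rates of 50 to 80%, falling to about 17 to 21% if lesioning is truly 5 points lower.
- Replace the unquantified statement of alike efficacy with a numeric assumption per arm, and reconcile it with the abstract's expectation on seizure freedom.
- Present impairment (2% v 11%) only as a secondary comparison, with exact-test power of about 75% one-sided or 66% two-sided. Re-basing 240 on an impairment superiority hypothesis chosen after the fact would leave the primary outcome without a justification.

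The cost is wording and, possibly, a less favourable stated power for efficacy. No extra patients are needed.

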### Data management

All baseline information and outcome-related data will be evaluated and collected by two experienced clinicians (one neurologist and one neurosurgeon). Detailed data collection and follow-up time are shown in Table 1. Each patient’s data will be completed into an electronic case report form (eCRF) by an independent clinical research coordinator. Participants will be given trial information to improve participation. In order to ensure the completion of the follow-up, we will contact participants by phone in advance.

**Table 1 Tab1:** Participant timeline

**Study period**	**Enrollment**	**Allocation**	**Operation**	**Follow-up**	**Follow-up**	**Follow-up**	**Follow-up**
**Time point**	− 10 days	− 7 days	0	7 ± 2 days	90 ± 7 days	180 ± 14 days	365 ± 14 days
**Participants**							
Eligibility screen	X						
Informed consent	X						
Randomization	X						
Demography		X					
**Interventions**							
MRI-guided stereotactic LITT group			X				
Stereotactic EEG-guided RF-TC group			X				
Resective surgery group			X				
**Outcomes**							
Seizure remission rate					X	X	X
Engel classification							X
ASMs		X		X	X	X	X
Neurological function examination		X		X	X	X	X
Scalp EEG		X			X	*X	X
NISHH		X					X
WAIS-IV-C/WCIS-IV-C		X					X
WADS-IV-C/WCDS-IV-C		X					X
QOILE-89/QOILE-48		X					X
PET		*X					*X
MRI		X			X	*X	X
Operative information			X				X
Adverse events				X	X	X	X

*X*, required; **X*, optional; *LITT* Laser interstitial thermal therapy, *EEG* Electroencephalography, *RF-TC* Radiofrequency thermocoagulation, *ASM* Anti-seizure medications, *WAIS-IV-C* Chinese version of the Wechsler Adult Intelligence Scale-IV, *WCIS-IV-C* Chinese version of the Wechsler Children’s Intelligence Scale-IV, *WAIS-IV-C* Chinese version of the Wechsler Adult Development Scale-IV, *WCIS-IV-C* Chinese version of the Wechsler Children’s Development Scale-IV, *QOLIE-89* Quality of Life in Epilepsy-89, *QOLIE-48* Quality of Life in Epilepsy-48, *PET* positron emission tomography, *MRI* Magnetic resonance imaging

All related data will be collected and entered into an eCRF and study database. The investigators and clinical coordinators will be responsible for ensuring that the required data are collected and entered into the eCRF. The original information will be kept in paper medical records for data traceability purposes. The eCRF will be printed as a paper version and stored in a dedicated locked filing cabinet.

Only authorized researchers will be allowed to process the research data under computer password protection. The final data will be anonymized by completely removing any participant’s identifying information.

### Quality control

The independent trial monitoring committee is responsible for quality control and interim analyses. The trial monitoring committee usually checks the status of the trial at the three centers on a monthly basis and presents the quality control results at a joint meeting that includes the investigators and clinical research coordinators. Quality control activities include the following:Request site support for study monitoring activities.Conduct unified training and assessment for the core research personnel of each center before the study begins.The study medical records and eCRF of the participants will be checked to confirm that the research team adhered to the protocol and that the data will be accurately recorded in the eCRF.Check that the completed eCRF is complete, of good quality, and properly stored.

If the monitor suspects that the study may not conform to the best protocol, specific measures should be taken to assess the situation, identify problems, and implement specific action plans to correct the situation. The trial is independently audited annually by the Beijing Municipal Health Commission.

### Ethics and communication

This study protocol has been approved by the Ethics Committee of Sanbo Brain Hospital, Capital Medical University (project number: SBNK-YJ-2022-006-01).

Modifications to the study protocol will be reviewed by the ethics committee. Important protocol modifications will be communicated to the Beijing Municipal Health Commission for approval before implementation. Written informed consent will be obtained from all participants before any patient data or patient information is collected. The progress and results of this study will be made publicly available on the ClinicalTrials.gov website. The results of this study will be disseminated through peer-reviewed publications and conference presentations. Authorship eligibility guidelines will be followed.

## Discussion

The randomized controlled trial can minimize the possible biases in the design and conduct of clinical trials. The conclusion of a well-designed and rigorously conducted randomized controlled trial is recognized as high-level evidence. To date, we have found no reports in the literature of randomized clinical trials of LITT and RF-TC for the treatment of focal DRE.

Epileptogenic focus resection is currently the most common and effective surgical treatment for focal DRE and is more likely to mean a radical cure. Among them, temporal lobectomy is the most common and has the best prognosis, while frontal lobectomy is the second most common [31–33]. Two randomized clinical trials of temporal lobe epilepsy found that patients treated with surgery were more likely to be seizure-free than those who continued medical therapy [28, 34]. However, it has been reported that resective surgery may lead to hemiplegia, memory impairment, visual field defect, and other complications [35, 36].

By selectively damaging a limited volume to the potential seizure initiation zone, stereotactic lesioning can limit the risk of neurologic impairment after surgery. However, despite the promising results, the seizure outcome after RF-TC and LITT is still not fully understood, with meta-analyses showing that seizure-free and responder rates varied widely across studies [25, 37, 38]. What is more, none of the studies included in the meta-analysis compared stereotactic injury with resective surgery. In addition, the predictors associated with postoperative outcomes remain unclear. Although some studies suggest that specific patient populations may achieve better outcomes, such as RF-TC-treated patients with periventricular nodular ectopia and LITT-treated patients with hypothalamic hamartoma. But to date, there have been few studies on the impact of the underlying etiology on the success rate of stereotactic lesioning. As mentioned above, there are still some deficiencies in the current research on stereotactic lesioning, which are the key issues of this study.

The protocol for this study was developed after careful discussion by MDT physicians in neurology, neurosurgery, neuroimaging, and neuropsychology. There was no patient or public involvement in the design of our study. We will do our best to perform our duties to provide reliable evidence for stereotactic lesioning in the treatment of epilepsy.

## Trial status

Recruitment ongoing (the first participant recruited on 20 September 2022, approximate recruitment completed date: December 31, 2023).

The protocol version is 1.0, and the version date is June 1, 2022.

## Data Availability

The progress and results of this study will be updated on the ClinicalTrials.gov website. The data set for this study could be obtained from the corresponding author after the study is completed for reasonable reasons. The full protocol can be shared with no restrictions on request.

## Abbreviations

RF-TC: Radiofrequency thermocoagulation
LITT: Laser interstitial thermal therapy
SEEG: Stereotactic electroencephalography
ASMs: Anti-seizure medications
DRE: Drug-resistant epilepsy
MRI: Magnetic resonance imaging
NISHH: National Institutes of Health Stroke Scale
EEG: Electroencephalogram
eCRF: Electronic case report form
